### Safety evaluation

AEs will be documented by researchers in case report form (CRF), including the date of onset and recovery, severity, relevance to the treatment, and how the AEs are resolved (or not). Treatment related AEs include dizziness, abscess, subcutaneous hematoma, local infection and other discomforts (i.e., fatigue, dizziness, or palpitations). If AEs do occur, the researchers will treat them appropriately, and notify the board who oversee data and safety of any severe ones. Then the board will assess whether the AEs are connected to the treatment and decide whether the study should be terminated or not. Frequency and percentage of patients suffering from AEs in three groups will be calculated.

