**Methods:**

This multi-center randomized controlled trial will enroll 360 patients with SUI. They will be randomly assigned to one of the three groups—sacral acupoints group (sacral group), abdominal acupoints group (abdominal group), or alternating acupoints group (alternating group)—at a 1:1:1 ratio. The patients will receive 18 sessions of EA treatment and will be followed up for 48 weeks after the treatment. The primary outcome measure of the study is the change of urine leakage at week 6. The secondary outcomes include the incontinence episode frequency (IEF), International Consultation on Incontinence Questionnaire-Short Form (ICIQ-SF), severity of SUI, patient self-evaluation of therapeutic effects, weekly usage of urine pads, ultrasonography of pelvic floor, specialty therapies for SUI, evaluation of discomfort during EA treatment, patient acceptability evaluation and adverse events related to intervention.

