**Figure 1 fig1:**
[figure not shown]
Flowchart. SUI, stress urinary incontinence; IEF, incontinence episode frequency; ICIQ-SF, International Consultation on Incontinence Questionnaire-Short Form; AEs, adverse events.

**Table 1 tab1:** Schedule of recruitment, interventions and assessments.

Study period	Enrolment		Intervention						Follow-up			
Time point	Week −1	Week 0	Week 1	Week 2	Week 3	Week 4	Week 5	Week 6	Week 18	Week 30	Week 42	Week 54
Inclusion/exclusion Criteria	**X**											
Sign informed consent	**X**											
Randomization	**X**											
*Intervention*												
Sacral acupoints treatment			**X**	**X**	**X**	**X**	**X**	**X**				
Abdominal acupoints treatment			**X**	**X**	**X**	**X**	**X**	**X**				
Alternating acupoints treatment			**X**	**X**	**X**	**X**	**X**	**X**				
*Primary outcome*												
Urine leakage		**X**						**X**				
*Secondary outcomes*												
Incontinence episode frequency		**X**				**X**		**X**	**X**	**X**	**X**	**X**
ICIQ-SF		**X**				**X**		**X**	**X**	**X**	**X**	**X**
Severity of SUI		**X**				**X**		**X**	**X**	**X**	**X**	**X**
Patient self-evaluation of therapeutic effects						**X**		**X**	**X**	**X**	**X**	**X**
Weekly usage of urine pads		**X**				**X**		**X**	**X**	**X**	**X**	**X**
Ultrasonography		**X**						**X**				
Specialty therapy for SUI									**X**	**X**	**X**	**X**
Evaluation of discomfort during treatment			**X**		**X**							
Patient acceptability evaluation			**X**		**X**							
Safety evaluation			**X**	**X**	**X**	**X**	**X**	**X**				

SUI, stress urinary incontinence; ICIQ-SF, International Consultation on Incontinence Questionnaire-Short Form.

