### Interventions

All treatments will be performed after skin disinfection. As acupuncture needles are inserted, all needles will be lifted, twisted, and stabbed to activate the sensation of “de qi.” The EA stimulation will last for 30 min with a continuous wave of 50 Hz and a current intensity of 1 to 5 mA (12). In the study, sterile acupuncture needles will be used, which are from Suzhou Medical Supplies Factory Co.’s Huatuo (size 0.30 × 75 mm). Patients will receive 3 treatments per week (every other day), for a total of 18 sessions over the course of 6 weeks. The follow-up sessions are in weeks 18, 30, 42 and 54. Besides, patients are told that they cannot use specialty therapy for SUI, such as pelvic floor muscle training, electrical stimulation, biofeedback, vaginal cone and medication during the 6 weeks treatment period.

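### Table 1 schedules safety evaluation only up to week 6, the week of the last needling session, so later-onset events and late recovery dates have no scheduled point of collection

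*Protocol article*

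**What the plan says.** The Interventions section sets the course: "Patients will receive 3 treatments per week (every other day), for a total of 18 sessions over the course of 6 weeks". It then places the later contacts: "The follow-up sessions are in weeks 18, 30, 42 and 54". The abstract gives the total length: "The patients will receive 18 sessions of EA treatment and will be followed up for 48 weeks after the treatment".

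In Table 1 the row "Safety evaluation" is marked at weeks 1, 2, 3, 4, 5 and 6. It is blank at weeks 18, 30, 42 and 54. The same four columns are marked for incontinence episode frequency, ICIQ-SF, severity, self-evaluation, pad use and specialty therapy.

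The Safety evaluation section lists the items to be recorded for each event, from onset and recovery dates to relatedness and resolution status: "AEs will be documented by researchers in case report form (CRF), including the date of onset and recovery, severity, relevance to the treatment". It names the expected events: "Treatment related AEs include dizziness, abscess, subcutaneous hematoma, local infection and other discomforts". The planned summary is: "Frequency and percentage of patients suffering from AEs in three groups will be calculated". The section gives neither a start nor an end for the recording of events.

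**The concern.** Three of the named events (abscess, local infection, subcutaneous hematoma) need not be visible on the day of needling, and they may take days to appear or clear. The plan asks for both onset and recovery dates. Yet the schedule stops asking about safety in the week in which the last three sessions are given, and asks at none of the four later contacts, although other outcomes are collected at each of them.

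At stake is the completeness of the safety comparison. If delayed events depend on patients reporting them unprompted, the percentage of patients with events in each group may be too low for exactly the event types that the article names. The recovery dates of events open at week 6 may stay blank.

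**Working it through.** **1. Timeline.** Inputs: 3 sessions per week and 18 sessions (Interventions); 48 weeks of follow-up (Abstract, Methods); contacts at weeks 18, 30, 42 and 54 (Interventions, Table 1).

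- Treatment length: 18 / 3 = 6 weeks, as the article states.
- End of follow-up: 6 + 48 = week 54, which agrees with the last column of Table 1.
- Gap from end of treatment to first follow-up contact: 18 − 6 = 12 weeks.

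**2. Safety row of Table 1, set against its header.**

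| Period | Columns | Safety marked |
|---|---|---|
| Treatment | weeks 1, 2, 3, 4, 5, 6 | 6 of 6 |
| Follow-up | weeks 18, 30, 42, 54 | 0 of 4 |

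The stretch without scheduled safety assessment is 54 − 6 = 48 weeks, or 48 / 54 = 89% of the time from week 0 to week 54. Most of that time is far from any needling, so this share describes the schedule and does not measure lost events. The part that matters is the period shortly after the last sessions.

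**3. Observation time after the last sessions (illustration under assumptions).** The article gives neither the days of the sessions nor the lag from needling to onset. Assume sessions on days 1, 3 and 5 of each week, so that the last three fall on days 36, 38 and 40, and assume that scheduled observation ends on day 42. A session has less than L days of scheduled observation if its day + L > 42.

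| Assumed lag L | Sessions affected | Share of 18 |
|---|---|---|
| 3 days | day 40 | 1/18 = 6% |
| 7 days | days 36, 38, 40 | 3/18 = 17% |
| 14 days | days 29, 31, 33, 36, 38, 40 | 6/18 = 33% |

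These are shares of sessions, not of events. Turning them into an understatement of the event percentage would need an event rate and a lag distribution, and the article gives neither.

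**4. The Safety evaluation section against Table 1.**

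- *Event with onset after the last session:* the section asks for its onset date, but Table 1 has no later point at which anyone is scheduled to ask.
- *Event with onset in weeks 1 to 6 and still open at week 6:* it is recorded, with its status as not resolved, because the listed items are "including the date of onset and recovery, severity, relevance to the treatment, and how the AEs are resolved (or not"). Only its later recovery date lacks a scheduled point.

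**The case against.** A reader might infer that adverse events are collected only in weeks 1 to 6, that late or unresolved events are therefore missed, and that the board never hears of them. The article does not support this. Table 1 schedules active assessment; it does not forbid recording an event that is reported later. The Safety evaluation section sets no end to recording, and its duty to notify the board of severe events has no time limit. An event open at week 6 is kept, as unresolved.

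Four further objections deserve weight.

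- The follow-up sessions are not said to be in person. What Table 1 collects there (diary items, questionnaire, self-rating, pad count, therapy use) could be obtained remotely, so it cannot be assumed that a patient is examined.
- The gap is the same in all three groups, and no bias in the comparison between them is shown.
- The article condenses a fuller protocol, and it refers to operating procedures and a data management plan that are not shown. An event window may be defined there.
- A safety question at week 18 comes too late to detect an infection in time to act on it, relies on recall, and falls in a period when specialty therapy is allowed.

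The first two points stand and limit the claim. The third does not remove it: the published schedule has a safety row that stops at week 6 while neighboring rows continue, so it is a stated choice rather than an omitted detail. If the full protocol sets a longer window, Table 1 needs to be aligned with it. The fourth is a fair limit on what the week 18 question can do, and it is why a stated recording interval with onset dates is needed as well.

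**Conclusion.** The point holds as a gap in scheduled ascertainment. Safety is assessed in all 6 treatment weeks and at none of the 4 follow-up contacts, with 12 weeks between the end of treatment and the first of them. New events after the last sessions, and recovery dates of events open at week 6, have no scheduled point of collection, so the per-group percentages may understate delayed events.

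The size of any understatement is unknown. Under the assumed session days and closure on day 42, between 1 and 6 of the 18 sessions have less scheduled observation than an assumed lag of 3 to 14 days; equally, 15 of 18 have at least 7 days. The conclusion itself rests only on the marks in Table 1 and the session schedule, not on those assumptions. It is worth correcting because the remedy is cheap. It does not threaten the primary analysis.

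**What to change.** 1. In Table 1, mark Safety evaluation at the existing week 18 follow-up contact.
2. In the Safety evaluation section, state that events with onset within a fixed interval after the last session are recorded, with the interval chosen by the sponsor. Require the onset date, so that events after the start of a specialty therapy can be separated from those that follow needling.
3. In the same section, state that an event open at week 6 has its outcome, and recovery date if any, recorded at the next scheduled contact.
4. If the full protocol already defines such a window, bring Table 1 into line with it.

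The cost is about one extra case report form page at a contact that is already planned, one table mark and two sentences of text. The downsides are recall over about 12 weeks at week 18 and possibly slightly higher reported event rates. No treatment or stopping rule is affected.

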### Sample size calculation

The PASS software (version 15.0.5, NCSS, LLC) was used to calculate sample size with *α* of 0.05 (two-tailed), power of 80%, and ratio of 1:1:1. Based on our previous research, the change of urine leakage between baseline and week 6 was calculated. For the sacral, abdominal, and alternating groups, the mean ± standard deviation (SD) was 9.90 ± 2.61, 10.30 ± 3.60 and 11.60 ± 3.93, respectively (12). Assuming a 20% dropout rate, the sample size is 120 patients for each group, and 360 patients in total.

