## Outcomes

The primary outcome of the study will be the change of urine leakage between baseline and week 6 measured by the 1 h pad test. The standardized procedure of the 1 h pad test requires the patients to wear a pre-weighed pad, drink 500 mL of water within 15 min, and then complete various activities including walking, going up and down stairs, standing and sitting, picking up a coin from the floor, coughing, running, and putting their hands under running water. Afterwards, the pad will be reweighed to measure the amount of urinary leakage (13). The 1 h pad test has a high adherence rate and a specificity of 65% to 89% (14). When patients have periods or a severe cough, outcome evaluations will be postponed and rescheduled until the end of the period or the remission of the cough.

The secondary outcomes include the following ten items:

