### Statistical methods

Statistical analysis, including a full analysis set based on intent-to-treat principle and a per-protocol set, will be conducted with SAS 9.4. Continuous variables described as mean ± SD or median (interquartile range) will be analyzed by *t*-test or rank-sum test while categorical variables represented by frequency (composition ratio) will be analyzed by chi-square or Fisher’s exact tests. Generalized estimating equation or mixed effect model is suitable for trends over time and treatment-time interactions. The analysis of correlation will be conducted with spearman correlation analysis. Exploratory subgroup analysis will be conducted to explore possible sources (i.e., parity status, the duration after the last childbirth, etc.) of heterogeneity and inconsistency. The confidence interval will be set at 95%, with a significance level of 5% (*p* < 0.05).

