It can be seen that the EA tolerance might be a key factor affecting the efficacy in EA treatment, but it has been rarely reported. Given that repeated stimulation of the same acupoints may lead to EA tolerance, we envisioned to provide treatments with alternating use of sacral and abdominal acupoints, which avoid the need to use the same set of acupoints every time. By adopting this approach, we aim to prevent EA tolerance caused by repeated stimulation, thus improving the clinical efficacy of the treatment.

In order to confirm the advantages of the treatment with alternating acupoints combination, a multi-center, stratified randomized study and a 48 weeks long-term follow-up with rigorous methodological design will be used to make the results more objective. In this study, the three groups will all receive acupuncture treatments (abdominal acupoints EA treatment, sacral acupoints EA treatment or alternating acupoints EA treatment), which encourage a better compliance of patients. On the other hand, we select BL33 and BL35 for the sacral group and RN3, RN4 and KI12 for the abdominal group. This is because our team’s previous investigations have demonstrated the effectiveness of EA using these acupoints in treating SUI (12, 19, 20). The positive outcomes may be attributed to EA’s capacity to address bladder neck and urethral support defects, modulate urinary bladder pressure, enhance urethral sphincter muscle tone, and reduce muscle fatigue (28–30). What’s more, the recovery of pelvic floor function is helpful for the treatment of SUI. Therefore, in addition to the use of the 1 h urinary pad test with standardized procedures, this study also used pelvic floor ultrasound for objective assessment of efficacy. At last, for medical ethical considerations, patients are allowed to receive specialty therapy for SUI during the follow-up period. The data will be collected as part of the secondary outcome, allowing us to compare the number of patients and frequency of use between the two groups. This analysis will not only offer insights into treatment effectiveness but also assess any potential sustained effects.

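### The stated 80% power is tied to no test or contrast; on the protocol's own planning values it does not hold for alternating versus abdominal (about 63% to 66%)

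*Protocol article*

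**What the plan says.** The sample-size section of the protocol article sets a significance level "of 0.05 (two-tailed), power of 80%, and ratio of 1:1:1". It gives planning values for the change in leakage from baseline to week 6 of 9.90 (SD 2.61) for sacral, 10.30 (SD 3.60) for abdominal and 11.60 (SD 3.93) for alternating, and ends: "Assuming a 20% dropout rate, the sample size is 120 patients for each group, and 360 patients in total". No test, common SD or pair of groups is named.

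The outcome being sized is the primary one: "The primary outcome of the study will be the change of urine leakage between baseline and week 6 measured by the 1 h pad test". In its Statistical methods section, the article says that continuous variables "will be analyzed by *t*-test or rank-sum test". It also mentions generalized estimating equations or a mixed model for time trends, but no analysis of variance or other overall three-group test. The Discussion describes the design as chosen "In order to confirm the advantages of the treatment with alternating acupoints combination".

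**The concern.** A t-test or rank-sum test compares two groups, so in a three-arm trial it implies pairwise comparisons. The aim concerns the alternating arm, so the natural pairs are alternating against each single combination. Of the two comparators, abdominal has the higher planning mean, which makes alternating versus abdominal the smaller difference (1.30, against 1.70 for sacral).

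An overall F test asks only whether the three means are all equal, and it can reject because alternating and sacral are far apart. If the 80% belongs to that test, it says little about alternating versus abdominal. A reader who applies the printed 80% to that contrast would overrate the trial's ability to detect the difference, and could take a non-significant result as evidence that alternating adds nothing over abdominal.

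**Working it through.** **Inputs (Sample size calculation section).** Means 9.90, 10.30, 11.60; SDs 2.61, 3.60, 3.93; two-sided 5%; 80% power; equal allocation; 20% dropout, so 120 × 0.8 = 96 completers per arm.

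**Step 1: reproduce 120 per arm.** One-way F test with three groups and common SD σ:
- Grand mean = (9.90 + 10.30 + 11.60)/3 = 10.60.
- Sum of squared deviations = 0.70² + 0.30² + 1.00² = 0.49 + 0.09 + 1.00 = 1.58.
- Noncentrality λ = n × 1.58/σ². With σ = 3.93 and n = 96, λ = 96 × 1.58/15.44 = 9.82.
- Power from the noncentral F with 2 and 285 degrees of freedom is 80.4%. At n = 95 it is 79.9%, so 96 is the smallest adequate n, and 96/0.8 = 120 exactly.

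The alternatives tried do not return 120:

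| Calculation | Completers per arm | Enrolled per arm |
|---|---|---|
| F test, SD 3.60 | 81 | 102 |
| F test, root-mean-square SD 3.43 | 73 | 92 |
| F test, mean SD 3.38 | 71 | 89 |
| Alternating vs sacral, two-sided (normal) | 61 | 77 |
| Alternating vs abdominal, two-sided (t) | 133 | 167 |
| Alternating vs abdominal, one-sided 5% | 104 | 130 |
| Abdominal vs sacral, two-sided (normal) | 970 | 1,213 |

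**Step 2: power of the alternating contrasts at 96 completers per arm.** SE = √((s₁² + s₂²)/n); noncentrality δ = difference/SE; power from the noncentral t, two-sided 5%, unadjusted.
- Alternating vs abdominal, stated SDs: SE = √((3.93² + 3.60²)/96) = 0.544; δ = 1.30/0.544 = 2.39; power 66.2%.
- Alternating vs abdominal, SD 3.93 in both: SE = 0.567; δ = 2.29; power 63%.
- Alternating vs sacral, stated SDs: SE = √((3.93² + 2.61²)/96) = 0.482; δ = 1.70/0.482 = 3.53; power 93.9%.
- Alternating vs sacral, SD 3.93 in both: δ = 1.70/0.567 = 3.00; power 85%.

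**Step 3: the same SD basis for every test.** With the stated group SDs, simulation puts the overall F test at 89.5% with 96 per arm.

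| SD basis, 96 per arm | Overall F test | Alternating vs sacral | Alternating vs abdominal |
|---|---|---|---|
| 3.93 throughout | 80% | 85% | 63% |
| Stated group SDs | about 90% | 94% | 66% |

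**Step 4: sensitivity for alternating vs abdominal.** With the stated SDs and all 120 per arm analysed, power is 76%. With the root-mean-square SD 3.43 in both arms it is 74% at 96 per arm and 83% at 120. With the stated SDs and alpha split over the two alternating contrasts (2.5% each), it is 55% at 96.

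**The case against.** The stated arithmetic can be reproduced, so a reader should not conclude that 120 per arm is miscalculated. Nor do the documents establish that an F test was used: the section names none, and both the test and the SD of 3.93 are inferred from the match.

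The protocol also sets no rule that alternating must beat both comparators. The Background describes an exploratory aim, and the wording about confirming an advantage comes from the Discussion. A reader might infer that the trial's real power is the 65% simulated for winning both comparisons. That would impose a success criterion the protocol does not state.

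The analysis sentence is a general list for all continuous variables in a condensed article; contrast order and primary model may be set elsewhere. An overall test followed by pairwise contrasts is an ordinary three-arm design, and its sample size would then fit its primary test. The full analysis set follows intention to treat, so more than 96 per arm may be analysed.

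These points limit the finding but do not remove it. The article prints a power figure without saying what it covers, and the only tests it names for continuous outcomes are ones for which the figure is not generally true. An analysis plan kept elsewhere would not change what the published 80% appears to promise.

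**Conclusion.** The point holds in a limited form. The 80% is unattached to any test. It fits an overall three-group F test at SD 3.93, and it does not hold for alternating versus abdominal: 66% with the stated group SDs and 63% with SD 3.93, at 96 completers per arm. These figures assume that the planning means are right and that the test is unadjusted, two-sided at 5%.

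Of the unadjusted cases computed, this contrast passes 80% only when the three SDs are pooled and nobody drops out. Both conditions are more favourable than what reproduces the protocol's own number.

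The shortfall is confined to this contrast; alternating versus sacral is adequately powered on either basis. It would be wrong to set the F test's 80% directly against 94% and 66%, because those figures use different SDs. The 167 per arm needed for 80% on this contrast (133/0.8 = 166.25, rounded up) shows the size of the gap. It does not show that the trial must be enlarged, since the protocol does not declare this contrast as its primary test.

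**What to change.** Keep 360 patients. Check the sample-size software output and state which test and SD the 80% refers to. If it was the overall F test, the section could read: 'With 96 completers per arm and a common SD of 3.93, the overall three-group F test has 80% power; on the same basis power is 85% for alternating versus sacral and 63% for alternating versus abdominal.' If the stated group SDs are preferred, the matching set is about 90%, 94% and 66%. The two sets should not be mixed.

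In the Statistical methods section, name the overall three-group test as the primary analysis that this sample size supports, followed by the two alternating contrasts, each with its 95% confidence interval. Requiring the overall test first costs little: in simulation with the group SDs, power for alternating versus abdominal is 65.6% with that step and 66.0% without it. Add that a non-significant alternating-versus-abdominal result will not be read as no difference.

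The cost is rewording two paragraphs and a less favourable stated power for one contrast. No extra patients or data are needed.
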